**Safety objectives**	
To evaluate the safety of SQSX for CCAD after PCI.	(1) Changes in routine tests of blood, urine, stool, and the function of the liver, kidney, and coagulation; (2) AEs.

### Adverse events

Adverse events (AEs) refer to negative or unanticipated clinical medical events that occur during the trial. The CCAD may lead to acute coronary syndrome, malignant arrhythmia, and other AEs. Patients will be rescued promptly and actively if the above happens. The details of AEs will be recorded and reported to the ethics committee.

### Data collection and management

An independent data manager will be responsible for data input and management. The case report form will be carefully archived and then integrated into the data management system. The double input, data cleaning, manual checks, and other methods will be conducted to verify the data's validity, correctness, and completeness.

### Investigator training and quality control

A Standard Operating Procedure (SOP) is prepared for researchers in each center. All researchers have been trained to ensure standardization. The training includes screening of eligible participants, usage of survey scales, performance of CPET, etc. The WeChat group will be used to connect patients closely. To ensure the quality, regular supervision will be executed by the quality control group and the monitors appointed by Xiyuan Hospital.

### Statistical analysis

An independent statistician will be responsible for data analysis. The enrolling results and the causes of missing data will be detailed. The efficacy analysis will be performed based on the intent-to-treat (ITT) and per-protocol (PP) populations. The ITT set consists of all participants randomized, and the PP set includes participants who follow the protocol exactly with an adherence rate of at least 80%. The primary outcomes, METS and Peak VO_2_ after 2 months of treatment, and the secondary outcomes, the change values of VO_2_/HR, AT, VE/VCO_2_ slope, several survey scales (SAQ, EQ-5D-5L, HAMA, FSS, etc.), TMAO, and hs-CRP from baseline to each visit, are both quantitative data. Others, including the incidence of MACCE and bleeding events, are qualitative data. The quantitative data will be presented as means ± SD, 95% confidence intervals, median and interquartile range. For inter-group comparison, if both groups meet the normal distribution with equal variance, the Student *t*-test will be applied, otherwise, the Wilcoxon rank sum test will be used. For within-group comparison, the Wilcoxon signed rank test or paired *t*-test will be adopted. The qualitative data will be described using frequency and rate. The Fisher's exact probability test and the McNemar test will be applied for inter-group comparison and within-group comparison, respectively. Confounding factors will be balanced using analysis of covariance if necessary. The linear mixed-effects model will be used to analyze longitudinal data. For safety analysis, the details of AEs will be tabulated and the incidence will be compared further. The above analysis will be conducted based on SAS software version 9.4. In all analyses, a two-tailed *P*-value < 0.05 will be regarded as statistically significant.

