### Sample size estimation

The sample size was estimated based on METS. The study showed that after 8 weeks of cardiac rehabilitation, the METS increased from 3.9 to 4.6 in CAD patients after PCI (27). We assumed the mean METS value of 3.9 for the control group and 4.1 for the intervention group after treatment, with a standard deviation of 0.3 METS. With the type I error rate set at 0.05 and the type II error rate at 0.1, a sample size of 49 is required for each group with the use of PASS version 11. We will include 60 participants in each group, assuming that 20% of the participants are lost to follow up.

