### Randomization and blinding

Stratified by center, sex, and age with a 1:1 allocation using random block sizes of 6, the randomization sequence was created using SAS software version 9.4. The investigators, patients and data analysts are blinded to the randomization sequence and treatment assignment. The emergency letter has been prepared, and the reason for opening the letter will be recorded if investigators break the blind.

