**Primary objective**	
To determine whether SQSX is superior to placebo in improving patient's CRF.	Changes in METS and Peak VO_2_ after treatment.

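### Primary comparison of METS and Peak VO2 is unadjusted by default, ANCOVA is left to an undefined condition, and the endpoint is a value in some places and a change in Table 3: valid but inefficient, and should be fixed in wording

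*Protocol article*

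**What the plan says.** All of this is in the protocol article.

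- **Endpoint as a value.** Statistical analysis names "The primary outcomes, METS and Peak VO_2_ after 2 months of treatment" and, in the same sentence, reserves change values for the secondary outcomes. The Primary outcome section also speaks of values. Sample size estimation assumes a "mean METS value of 3.9 for the control group and 4.1 for the intervention group after treatment, with a standard deviation of 0.3 METS".
- **Endpoint as a change.** Table 3, under the primary objective, gives "Changes in METS and Peak VO_2_ after treatment".
- **Test.** Quantitative outcomes are compared by Student t-test if both groups look normal with equal variance; "otherwise, the Wilcoxon rank sum test will be used".
- **Adjustment.** "Confounding factors will be balanced using analysis of covariance if necessary". No covariate is listed and no condition is given.
- **Randomisation.** "Stratified by center, sex, and age with a 1:1 allocation".
- **Baseline data.** Table 2 schedules the cardiopulmonary exercise test at Visit 1 and again at Visit 3, so each primary outcome has one baseline and one post-treatment measurement.
- **Mixed model.** Statistical analysis assigns a linear mixed-effects model to longitudinal data without naming outcomes or covariates.

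**The concern.** Three features of the plan act together on the primary comparison.

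1. Baseline METS and Peak VO2 are collected but enter no analysis that the plan commits to. The same holds for center, sex and age, although randomisation is stratified on them. Precision that is already paid for is left unused. After stratified randomisation, an unadjusted t-test also has a standard error that is too large, because between-strata variance stays in the error term.
2. The 2-month value and the change from baseline are different test variables with different variances. Which one is meant affects power, and the article says both.
3. An adjustment made only when judged necessary, with no stated criterion, can be decided after outcomes have been seen. In a randomised trial, covariates are better chosen in advance for their prognostic value than afterwards for apparent imbalance.

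The pre-test for normality and equal variance adds a smaller problem. If variances differ, the analysis moves to Wilcoxon, which does not test the difference in means on which the trial is powered. The mixed-model sentence does not settle the matter, since it is not tied to the primary outcomes and these have a single post-baseline measurement.

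**Working it through.** **Inputs from the documents.** Difference 4.1 − 3.9 = 0.2 METS, SD 0.3, and the error rates: "With the type I error rate set at 0.05 and the type II error rate at 0.1, a sample size of 49 is required" per group. The test is two-sided: "a two-tailed *P*-value < 0.05 will be regarded as statistically significant". The plan has 60 per group with 20% loss, which leaves 60 × 0.8 = 48 evaluable.

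**Inputs assumed.** The correlation r between baseline and 2-month METS is not in the article; 0.3, 0.5 and 0.7 are shown, with equal SDs at both times. The number of strata is not given, because age cut-points are not stated; 4 centers × 2 sexes × 2 age bands = 16 is assumed. The share of outcome variance explained by the strata is assumed to be 5% to 40%.

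**Step 1: the plan's own figure.** The noncentral t calculation for an unadjusted two-group comparison of values gives power 90.4% at 49 per group and 89.8% at 48. The stated 49 is reproduced, and it belongs to a two-sided, unadjusted test of the post-treatment value.

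**Step 2: effective SD under each analysis.**
- 2-month value: SD = 0.3
- change score: SD × √(2(1 − r))
- ANCOVA on baseline: SD × √(1 − r²)

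**Step 3: power at 48 per group, difference 0.2.**

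| Assumed r | Change SD | ANCOVA SD | Value | Change | ANCOVA |
|---|---|---|---|---|---|
| 0.3 | 0.355 | 0.286 | 89.8% | 78.0% | 92.3% |
| 0.5 | 0.300 | 0.260 | 89.8% | 89.8% | 96.2% |
| 0.7 | 0.232 | 0.214 | 89.8% | 98.7% | 99.5% |

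The change score is weaker than the value when r is below 0.5 and stronger above it. ANCOVA is more precise than both at each r shown.

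**Step 4: ignoring the strata.** With perfect balance within strata that explain a share R² of the variance, the true two-sided level of the unadjusted test is about 2 × (1 − Φ(1.96/√(1 − R²))). For R² = 0.10 this is 3.9%, and for R² = 0.20 it is 2.8%. Incomplete blocks of 6 in small strata weaken the balance. Simulation with 16 strata therefore gives a milder result: about 4.5% at R² = 0.05, falling to about 2.1% at R² = 0.40. The error is on the conservative side throughout.

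**Step 5: the t-test/Wilcoxon switch.** The rule was simulated with Shapiro and Levene pre-tests, 48 per group and equal means of 3.9. It rejects about 5% of the time with normal data and SD 0.3 in both arms, and about 5% to 6% with SD 0.3 against 0.48, whether normal or lognormal. At the plan's dispersion the switch does no material harm to the error rate. Its fault is that the question tested depends on a pre-test.

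**Step 6: value and change under ANCOVA.** Let Y be the 2-month value, B the baseline and T the treatment. If Y = a + τT + βB + e, then Y − B = a + τT + (β − 1)B + e. The treatment coefficient τ is the same, so baseline adjustment removes the conflict between the two endpoint wordings.

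**The case against.** The strongest reply is that nothing here makes the primary test invalid. The sample size was computed for the very comparison that Statistical analysis names, and 89.8% at 48 evaluable per group is the planned 90% to within rounding. All the gains from ANCOVA rest on a correlation that the article does not give. The move to Wilcoxon follows a written rule. Data analysts are blinded to assignment (Randomization and blinding), and an independent statistician does the analysis. A covariate list is often left to a statistical analysis plan, which is not shown. On the endpoint, Table 3 is the only place that says change.

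Most of this stands, and it limits the point in three ways.

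- A reader might infer that the plan inflates false positives because an analyst could try value and change and report whichever is significant. That would give about 9% to 10% in simulation. The article does not describe such a practice, and blinded analysts make it harder, so this is not a property of the plan.
- A reader might infer that the switching rule inflates error. Very skewed data with very unequal variances can produce that, but the plan's mean and SD (0.3/3.9, about 8%) are nowhere near such dispersion, and Step 5 shows about 5% to 6%.
- A reader might take the stratification problem as a threat to validity. It works in the opposite direction.

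The reply does not dispose of the rest. The article does not simply leave the model to another document: it commits to unadjusted tests, makes adjustment conditional on an unstated judgement, and states the primary endpoint in two ways. Blinding reduces the risk of a convenient choice but does not define the choice.

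**Conclusion.** The point holds as an efficiency and prespecification weakness, not as a validity failure; it should be fixed. On the plan's own inputs the unadjusted comparison of 2-month values keeps its error rate and essentially its planned power. It gives up precision: ANCOVA would raise power from 89.8% to between 92.3% and 99.5% for r between 0.3 and 0.7. It is also somewhat conservative, with a true level of about 4.5% to 2.1% under the assumed strata. The endpoint wording matters because an unadjusted change score, as Table 3 could be read, would have 78.0% to 98.7% power over the same range, below target if r is under 0.5. These figures are for METS only; the article gives no planning values for Peak VO2. They depend on the assumed r, on equal SDs at both visits, and for the level on the assumed number and strength of strata.

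**What to change.** - For both METS and Peak VO2, prespecify one primary analysis: ANCOVA of the 2-month value on treatment, that outcome's own baseline value, center, sex and age, with heteroscedasticity-robust standard errors. Report the adjusted mean difference with its 95% confidence interval. Both outcomes keep their primary status.
- For these outcomes, delete the clause that makes ANCOVA conditional, and delete the normality and equal-variance gate. Wilcoxon may stay as a sensitivity analysis.
- Reword the primary row of Table 3 to the 2-month value adjusted for baseline, so that it agrees with the Primary outcome and Statistical analysis sections.

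The cost is wording in the protocol and any analysis plan, made before unblinding. No additional patients, visits or measurements are needed, and the sample size can stand.

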### Exclusion criteria

Patients should be excluded if any of the following exclusion criteria are fulfilled:

(1) Renal insufficiency (serum creatinine >220 umol/l for males or >175 umol/l for females);(2) Severe liver disease or elevated alanine transaminase (ALT) and aspartate transaminase (AST) (≥3 times upper limit of normal);(3) Controlled systolic blood pressure or controlled diastolic blood pressure >160/100 mmHg, respectively;(4) Glycosylated hemoglobin ≥9.5% or random blood glucose ≥13.7 mmol/L in diabetics;(5) Women who are pregnant, are breastfeeding, or are planning to become pregnant;(6) Acute or chronic severe cerebrovascular disease;(7) Malignancies;(8) Severe hematopoietic disorders;(9) Severe mental illness;(10) Intestinal inflammatory or malabsorptive disorders;(11) Patients who have participated in other studies within 3 months.

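### AE incidence is to be judged by rates and a P-value without an interval, so at 60 per arm a non-significant comparison could not exclude a material excess of harm

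*Protocol article*

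**What the plan says.** Table 3 of the protocol article sets a separate safety objective, "To evaluate the safety of SQSX for CCAD after PCI", with two kinds of measure: laboratory changes and AEs.

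The Statistical analysis section gives AEs one sentence: "For safety analysis, the details of AEs will be tabulated and the incidence will be compared further". The general rules of that section supply the rest:

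- Summary of categorical data: "The qualitative data will be described using frequency and rate".
- Test for categorical data: "The Fisher's exact probability test and the McNemar test will be applied for inter-group comparison and within-group comparison, respectively".
- Significance level: "In all analyses, a two-tailed *P*-value < 0.05 will be regarded as statistically significant".
- Summary of quantitative data: "The quantitative data will be presented as means ± SD, 95% confidence intervals, median and interquartile range".

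So intervals are named for quantitative data and not for categorical data. The section classes MACCE and bleeding incidence as categorical, so bleeding falls under the same rule. The Sample size estimation section rests on METS only and makes no statement about safety.

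**The concern.** A comparison of AE incidence with about 60 patients per arm gives a weak yes-or-no answer. If the output is two rates and a P-value, the likely result for a doubling or tripling of a low AE risk is a non-significant difference. The question a safety objective poses is different: how large an excess on SQSX is still compatible with the data? The planned output does not answer it, although the data allow an answer and the same section already uses intervals for quantitative outcomes. At stake is whether the final report can say anything quantitative about excess harm, and whether its readers are left to draw that conclusion from a P-value.

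**Working it through.** **Inputs from the protocol article.** 60 per arm, 1:1; assumed loss 20%, so 60 × 0.8 = 48 per arm; Fisher's exact test; two-sided 0.05. **Assumptions, because the article gives no AE rates:** the risk pairs and the observed counts used below.

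**1. The plan's own figure.** Difference 4.1 − 3.9 = 0.2 METS, SD 0.3, 90% power. The normal approximation gives n = 2 × (1.960 + 1.282)² × 0.3² / 0.2² = 47.3, so 48. With the noncentral t distribution, power is 0.898 at 48 and 0.904 at 49, so the stated 49 per group is reproduced. It concerns METS only.

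**2. How often Fisher's test misses an excess.** Power is the sum, over all pairs of counts (a, b) with Fisher P < 0.05, of Bin(a; n, p_placebo) × Bin(b; n, p_SQSX). The miss rate is 1 − power.

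| Assumed risk, placebo vs SQSX | Power, 60 per arm | Missed, 60 per arm | Missed, 48 per arm |
|---|---|---|---|
| 10% vs 30% | 73.0% | 27% | 39% |
| 5% vs 20% | 62.7% | 37% | 52% |
| 5% vs 15% | 32.6% | 67% | 77% |
| 10% vs 20% | 24.7% | 75% | 82% |
| 5% vs 10% | 8.8% | 91% | 94% |
| 0% vs 5% | 7.9% | 92% | 97% |
| 2% vs 6% | 5.5% | 95% | 97% |

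The last column is pessimistic: it treats every lost patient as contributing no AE data.

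**3. What an interval would add.** The Newcombe 95% interval for the risk difference d = p₂ − p₁ (SQSX minus placebo) is built from the Wilson limits (l₁, u₁) and (l₂, u₂) of the two arms:

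- lower = d − √[(p₂ − l₂)² + (u₁ − p₁)²]
- upper = d + √[(u₂ − p₂)² + (p₁ − l₁)²]

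For 3/60 the Wilson limits are 0.0171 and 0.1370. With 3/60 in both arms, d = 0 and the upper limit is √[(0.1370 − 0.05)² + (0.05 − 0.0171)²] = √(0.00757 + 0.00108) = 0.093, that is +9.3 points.

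| Placebo | SQSX | Fisher P | Difference, points | Newcombe 95% interval, points |
|---|---|---|---|---|
| 3/60 | 3/60 | 1.00 | 0 | −9.3 to +9.3 |
| 3/60 | 8/60 | 0.20 | +8.3 | −2.5 to +19.7 |
| 3/60 | 9/60 | 0.13 | +10.0 | −1.1 to +21.6 |
| 3/60 | 10/60 | 0.075 | +11.7 | +0.3 to +23.5 |
| 3/60 | 11/60 | 0.043 | +13.3 | +1.7 to +25.4 |

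Against 3/60 on placebo, Fisher's test needs 11/60 on SQSX to reach P < 0.05. At 10/60 it is not significant, although the Newcombe interval already lies above zero. For an event never seen in an arm of 60, the exact two-sided 95% upper limit is 1 − 0.025^(1/60) = 6.0%.

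**The case against.** The strongest reply is that little here is an error. The trial is sized on METS and claims no power for AEs; low power for AEs is usual in such a trial and conflicts with no stated figure. The article is condensed, and risk differences with intervals may sit in an analysis plan that is not shown. Counts with denominators let any reader compute the interval. The risk pairs are assumptions, and a large excess such as 10% against 30% would be detected about 73% of the time.

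Most of this stands. It limits the point to the method that the article does state. On AEs it is not silent: it prescribes a comparison, a test, a significance level and a descriptive summary, and it names intervals for the other data type. An analysis plan written to match would produce rates and a P-value.

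Two stronger readings are tempting and are not supported. A reader might infer that a non-significant AE result will be reported as showing safety. No sentence says so, and the Table 3 objective is neutrally worded. A reader might also infer that the safety objective rests on this one test. It does not: its measures are "1) Changes in routine tests of blood, urine, stool, and the function of the liver, kidney, and coagulation; (2) AEs", AE details are to be tabulated, and numeric laboratory results, if handled as quantitative data, would have 95% intervals.

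**Conclusion.** The point holds in a limited form. For AE incidence the stated method gives rates and a two-sided test at 0.05, without an interval, and at 60 per arm a non-significant result could not exclude a material excess. Under assumed risks of 5% and 15% the test misses the excess about 67% of the time. Over the other pairs tried, the miss rate runs from about 27% (10% vs 30%) through 92% (0% vs 5%) to 95% (2% vs 6%). These rates depend wholly on the assumed risks. The interval results depend only on the illustrative counts: equal counts of 3/60 leave +9.3 points as the upper limit.

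This is a weakness in what will be reported. It is not a mistaken calculation, it calls for no larger sample, and it shows no intention to claim safety from non-significance. It also does not require changing the Table 3 objective or counting laboratory values against the exclusion limits, which the article sets for entry only.

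**What to change.** In the Statistical analysis section, replace the safety sentence with wording such as:

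*The incidence of AEs, serious AEs and bleeding will be reported by arm and as the SQSX minus placebo risk difference with a 95% confidence interval (Newcombe). The safety statement will be based on the upper confidence limit of the excess risk. A non-significant P-value will not be taken as evidence of no harm.*

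Fisher's test may stay as a descriptive addition. Because it can disagree with the interval (10/60 against 3/60), the text should say that the interval governs.

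The change uses data already collected and adds a few table columns; it needs no new visits or patients. Its one small downside is that wide limits will be visible, so the safety statement will look less favourable than a bare non-significant result.

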## Discussion

The treatment for CCAD appears to be trapped. Currently, most studies on CCAD have focused on the strategies and medical devices for revascularization, including preferential choice of PCI or coronary artery bypass grafting (CABG), novel supreme drug-eluting stents, intravascular ultrasound-guided treatment, etc., (25, 35–37). Even with the help of state-of-the-art revascularization, the improvement in myocardial ischemia is usually regional and limited. With strict adherence to evidence-based secondary prevention of CAD after PCI, the severe threats of high incidence of MACCE and low quality of life are still facing patients with CCAD (38, 39). To our knowledge, there are no viable therapies or preventative strategies for these conditions. Our previous studies have confirmed that SQSX has the favorable effects of improving angiogenesis and preventing in-stent restenosis. The Chinese herbal formula with multi-target characteristics has the potential to provide a promising therapeutic strategy for CCAD after PCI. Thus, tailored to the unique population of CCAD, this multi-center, randomized, double-blinded, parallel, placebo-controlled clinical study uses CPET, several survey scales, and other methods to evaluate the efficacy and safety of SQSX.

There are two limitations to this work. First, as a surrogate indicator, CRF doesn't directly represent the real influence on MACCE. In the future, the clinical endpoint of MACCE will be used as the primary outcome measure to conduct clinical research. Second, CCAD includes a variety of lesions, such as multivessel disease, left main lesions, chronic total occlusion lesions, etc. The differences between various lesions of CCAD may affect the result of the trial. Thus, the subgroup analysis will be performed to minimize the impact of these differences.

To conclude, this study is launched to evaluate the efficacy and safety of SQSX in CCAD after PCI and probe the possible mechanism.

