### Inclusion criteria

The study will include patients who satisfy all of the following inclusion criteria:

(1) Diagnosis of CCAD based on one or more of the following coronary artery lesions (28–30):

Bifurcation lesions (side branch diameter >2.0 mm);Excessive tortuosity of proximal segment;Severe coronary artery calcification;Chronic total occlusion lesions (>3 months);Left main lesion;Aorto-ostial lesions;Diffuse lesions (>20 mm length);Multivessel coronary artery stenosis (≥2 two vessels);Extremely angulated lesions (>90° bend);In-stent restenosis.

(2) Diagnosis of stable angina according to the 2019 ESC guidelines (31);(3) NYHA class I-III;(4) At least one stent was implanted within 2 years;(5) 18 years ≤ age ≤ 75 years;(6) Diagnosed as the traditional Chinese medicine (TCM) syndrome of the Qi deficiency in the heart and spleen according to an array of specific symptoms, including chest tightness, abdominal distension, appetite loss, fatigue, and lassitude, with a pale tongue and a white greasy coating, etc., (32);(7) No antibiotics, hormones, laxatives, antidiarrheals, or probiotics have been used within 3 months;(8) Written informed consent is obtained.

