#### Secondary outcomes

The first of the secondary outcomes are other indicators of cardiopulmonary exercise testing (CPET), including the oxygen pulse (VO_2_/HR), the anaerobic threshold (AT), and the slope of ventilatory equivalent for carbon dioxide (VE/VCO_2_ slope), etc. The additional secondary outcomes are: (1) EQ-5D-5L; (2) SAQ; (3) FSS; (4) HAMA; (5) the blood stasis syndrome score (BSSS) (34); (6) echocardiography; (7) electrocardiography; (8) TMAO; (9) high-sensitivity C-reactive protein (hs-CRP); (10) MACCE and bleeding events. Furthermore, metagenomic sequencing will be performed to probe possible changes to the structure of intestinal flora after treatment. The plasma and stool samples will be collected and stored in the laboratory freezer (−80°C) for future TMAO testing and metagenomic sequencing.

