**Secondary objectives**	
To determine whether SQSX is superior to placebo in improving patient's CRF.	Changes in other indicators of CPET, including VO_2_/HR, AT, and VE/VCO_2_ slope, etc. after treatment.
To compare the effect of SQSX vs. placebo on quality of life based on several survey scales.	Changes in scores measured by EQ-5D-5L, SAQ, FSS, and HAMA from baseline.
To compare the effect of SQSX vs. placebo on TCM syndrome.	Change in BSSS from baseline.
To assess cardiac structure and function with echocardiography and electrocardiography.	Results will be reported separately.
To explore the possible impact of SQSX on TMAO.	Change in TMAO after treatment.
To explore the possible impact of SQSX on hs-CRP.	Change in hs-CRP after treatment.
To depict intestinal flora features of CCAD and explore possible changes induced by SQSX.	Changes to the structure of intestinal flora after treatment using metagenomic sequencing.
To determine whether SQSX is superior to placebo in reducing the incidence of MACCE and bleeding events.	Time to the first occurrence of any of the components of this composite: (1) death; (2) non-fatal myocardial infarction; (3) ischemic stroke; (4) bleed.

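### Lesion-type subgroup analysis cannot remove the effect of lesion mix on the overall result, and the blanket P<0.05 rule covers subgroup and metagenomic comparisons without exception

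*Protocol article*

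**What the plan says.** The second limitation in the protocol article's Discussion is that complex coronary disease covers many kinds of lesion, which may affect the trial's result. The remedy given is: "Thus, the subgroup analysis will be performed to minimize the impact of these differences". Three lesion types are named there as examples, with an open-ended list implied.

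The Inclusion criteria list ten lesion types and admit a patient on any of them: "Diagnosis of CCAD based on one or more of the following coronary artery lesions". Lesion type plays no part in the allocation, which is "Stratified by center, sex, and age with a 1:1 allocation using random block sizes of 6". The Statistical analysis section compares groups by Student t-test or Wilcoxon rank sum test. It keeps analysis of covariance in reserve for confounders, should it be thought needed, and names no covariate.

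The same section ends with a general rule: "In all analyses, a two-tailed *P*-value < 0.05 will be regarded as statistically significant". Among the comparisons within its reach is the flora work, where "metagenomic sequencing will be performed to probe possible changes to the structure of intestinal flora after treatment". The matching objective in Table 3 is worded as exploratory: "To depict intestinal flora features of CCAD and explore possible changes induced by SQSX".

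**The concern.** Two statements are at issue, and both are things the article says rather than things it leaves out.

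First, the method does not serve the stated purpose. If lesion types differ in prognosis, their mix adds noise to the overall comparison and can differ between arms by chance. Stratification or covariate adjustment deals with that. Subgroup analysis answers another question, namely whether the treatment effect differs between kinds of patient, and the overall estimate is the same number before and after it. The Introduction suggests that lesion type matters: it gives 10-year mortality of 21%, 27.6% and 28% for three-vessel disease, chronic total occlusion and left main lesions, against 18.6% for general lesions. These are mortality figures, not METS, so they support prognostic relevance but not its size here.

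Second, a single significance threshold for every analysis gives a subgroup or metagenomic P-value the same standing as the primary one. At stake are later claims about which patients benefit and by what mechanism, which could rest on small, overlapping subgroups or on chance findings among many features.

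**Working it through.** **Inputs.** From Sample size estimation: "We assumed the mean METS value of 3.9 for the control group and 4.1 for the intervention group after treatment" (so a difference of 0.2), SD 0.3, type I error 0.05, type II error 0.1, 60 per arm with 20% loss. From Inclusion criteria: ten overlapping lesion types. From Statistical analysis: two-sided 0.05 throughout. The number of metagenomic features is not given, so any figure for it is an assumption.

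**1. The plan's own figure.** Normal approximation: n = 2 × (1.960 + 1.282)² × 0.3² / 0.2² = 47.3, so 48 per arm. The exact noncentral t calculation gives power 0.898 at 48 and 0.904 at 49, so 49 per arm is reproduced. The same power function is used below.

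**2. What lesion mix does to the overall estimate.** With two lesion classes and a common treatment effect, the expected difference in means for a given allocation is the treatment effect plus (difference between arms in the proportion in class A) × (difference in mean METS between the classes). Randomization makes the second term zero on average but not in any one trial. Adjusting for class removes it. Reporting each class separately leaves the overall figure as it was. The article gives no METS values by lesion type, so the size of this term cannot be computed.

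**3. Power inside a subgroup.** With n per arm, the noncentrality is 0.2 / (0.3 × √(2/n)) on 2n − 2 degrees of freedom, two-sided 0.05:

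| n per arm in subgroup | Power for 0.2 METS |
|---|---|
| 30 (half of those enrolled) | 72% |
| 24 (half of 60 × 0.8 = 48 evaluable) | 62% |
| 20 | 54% |
| 10 | 29% |

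An interaction test has less power still. For two equal classes whose effects differ by 0.2 METS, the standard error is 0.3 × √(4/n). By normal approximation the power is 45% at n = 30 per arm per class and 37% at n = 24.

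**4. Chance of at least one false positive.** For k independent tests at 0.05 with no true effect, this is 1 − 0.95^k:

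- k = 3 (the three lesion types named in the Discussion): 14.3%
- k = 10 (every listed type): 40.1%
- k = 20 (ten types × two primary outcomes): 64.2%
- for 95%, k = ln 0.05 / ln 0.95 = 58.4, so 59 tests
- for 99%, k = ln 0.01 / ln 0.95 = 89.8, so 90 tests

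**5. Dependence between tests.** Overlapping subgroups and correlated outcomes lower these figures. Simulated equicorrelated tests at correlation 0.3, 0.5 and 0.7 give 36%, 29% and 21% for k = 10, and 53%, 42% and 29% for k = 20. For an assumed 200 features they give 99.4%, 90% and 60%. The expected number of false positives, 0.05 × 200 = 10, does not change with correlation.

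**The case against.** The strongest reply is that the sentence is a remark on limitations, not part of the analysis section, and that subgroup definitions, interaction tests and false-discovery methods usually sit in an analysis plan that is not shown. That is right as to the missing detail, which is not counted here. It does not rescue the two statements: the purpose given for subgroup analysis is wrong whatever an analysis plan adds, and an analysis plan with false-discovery control would conflict with the published rule, which makes no exception.

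A second reply is that allocation is random and covariance analysis is available. Both are true. A reader might infer that the treatment comparison is biased by lesion mix, or that adjustment has been ruled out. The article supports neither. Lesion mix costs precision and allows chance imbalance, and adjustment is left to an unspecified judgement of need.

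Third, a reader might infer that chance positives are close to certain. For the subgroups this does not follow. For the flora, the article speaks of its structure, which could mean a few community-level summaries, and it states neither a feature count nor a taxon-level test. One might also divide 120 by ten to get 6 per arm, with 18% power. That assumes each patient has exactly one lesion type, which the entry criteria do not require; overlap makes the subgroups larger. Nor does a 56% chance of a false positive over about 16 secondary comparisons hold as a firm figure, since it treats repeated scores on the same patients as independent and ignores the planned mixed-effects model.

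**Conclusion.** The point holds for both statements. Subgroup analysis will not reduce the influence of lesion mix on the overall result, and nothing else in the article commits to doing so. Subgroup results would also be weak evidence: even half of the enrolled patients give about 72% power for the design effect, and smaller subgroups much less.

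Under the blanket rule, the chance of at least one spurious subgroup finding is 14% to 64% for independent tests, depending on how many are run, and lower if they are correlated. This range rests on assumed counts of 3 to 20 tests, because the article does not say how many subgroups there will be. A figure of 95% or more needs about 59 independent tests, which only taxon-level metagenomic testing could plausibly supply. That remains a conditional statement.

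The sample size and the validity of the primary randomized comparison are not affected. This is a should-fix matter of stated method and claim.

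**What to change.** - **Discussion.** Replace the sentence with a sensitivity analysis: ANCOVA of METS and of Peak VO2 at 2 months, adjusted for the baseline value and a prespecified lesion class (for example left main, chronic total occlusion or multivessel disease versus other). Lesion type has to be established at screening to confirm eligibility, so no new data are needed.
- **Subgroups.** Call them exploratory, use a few disjoint classes, and judge them by a treatment-by-class interaction with confidence intervals. Given the interaction power of 37% to 45% above, state that a non-significant interaction does not show a uniform effect.
- **Significance rule in Statistical analysis.** Limit the P<0.05 claim to the primary analysis, and report secondary and subgroup results as estimates with confidence intervals. Apply Benjamini-Hochberg false-discovery control to any taxon-level tests. This does not settle how the two primary outcomes share the 5%, which is a separate question.

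The cost is a little more analysis and fewer nominally significant exploratory results. Sample size, visits and treatment are unchanged.
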